### Primary outcome evaluation

#### Recruitment feasibility

Recruitment feasibility will be assessed through the reach or number of participants we are able to recruit from the local area and surrounding town into the trial. Additionally, we will determine the length of time required to recruit 40 eligible participants.

#### Intervention delivery feasibility and acceptance

Intervention delivery feasibility will be assessed based on several metrics. We will determine the percentage of wellness coaching sessions delivered and completed within the home setting of each participant via coach self-report, following each session. The fidelity of the intervention delivery components will be determined based on whether or not primary and secondary activities were performed during the home-based sessions. Any adverse effects related to intervention delivery will be collected via coach report. Intervention acceptance will be measured through parent and participant satisfaction questionnaires, which will be completed during a post-intervention interview. These metrics for feasibility will allow us to assess whether or not the wellness coaching intervention can be delivered according to a weekly schedule and whether the intervention is accepted by participants and parents.

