**Methods/design:**

Forty girls who are overweight or obese (aged 8–13 years) will be recruited from a Midwestern college town. Participants will be recruited through posted flyers, newspaper advertisements, email, and social media. The volunteer convenience sample of girls will be randomized to one of two home-based wellness coaching interventions: a general health education condition or a healthy eating physical activity skills condition. Trained female wellness coaches will conduct weekly hour-long home visits for 12 consecutive weeks. Assessments will occur at baseline, post-intervention (3 months after baseline), and follow-up (6 months after baseline) and will include height, weight, waist circumference, body composition, pulmonary function, blood pressure, systemic inflammation, physical activity (Actical accelerometer), and self-reported survey measures (relevant to fruit and vegetable consumption, physical activity, and quality of life).

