Both boys and girls are impacted by problems associated with obesity and could benefit from interventions and programs targeting health promotion. Girls, in particular, may do well with targeted health promotion and obesity prevention programs for a number of reasons. First, they are less physically active than boys, and this comparison becomes more disparate with increasing age, not only in terms of overall amount of physical activity but also in vigorous intensity physical activity [11]. Second, overweight and obese adolescent girls are more likely than healthy weight girls to use dysfunctional methods to try to control their weight [12]. Given the dysfunctional weight control efforts and special concerns within this population, it makes sense to develop health promotion and obesity prevention interventions that are uniquely tailored to meet the needs of girls.

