## Methods/design

### Study design

As shown in Fig. 1, this study is a two-arm, parallel randomized trial comparing two home-based coaching interventions on primary feasibility outcomes related to recruitment, intervention delivery and acceptance, and health outcome assessments, with secondary, preliminary measures related to health-related psychosocial, behavioral, and biomedical outcomes of female children. The home-based, wellness coaching intervention period will last for 12 weeks, with laboratory assessments at baseline, post-intervention (3 months after baseline), and at follow-up (6 months after baseline). A 6-month follow-up period was chosen to evaluate the feasibility of having participants return to the laboratory for an assessment following the conclusion of the intervention. A fully powered study examining the impact on health outcomes may employ a longer-term follow-up to assess maintenance of behavior change and subsequent changes in health outcomes.

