### Wellness coaching interventions

For both the HEPA skills and HE coaching intervention conditions, college-aged female research assistants will undergo ethics training, plus three 1-h coach training sessions, to serve as wellness coaches and deliver 12 weekly one-on-one intervention sessions in the home of each participating child. Materials and lessons for the wellness coaching curriculum are adapted from “Health in the Classroom” [28] and other supporting educational materials as appropriate to the topic and age group of the client. The theoretical basis for the intervention development comes from social cognitive theory [29] and the self-determination theory [30]. Social cognitive theory posits that behavior, personal factors, and the environment have reciprocal effects on one another to determine human behavior. Within this intervention, personal factors targeted are self-efficacy, observational learning, and monitoring and regulation of behavior. Constructs from the self-determination theory include autonomy, relatedness, and competence, which are also targeted within both arms of the intervention. Training will take place before coaching sessions 1, 5, and 9. The wellness coach and parent will mutually agree upon meeting times, so that at least one parent is always present in the home during the session, although the parents will not be involved in the coaching sessions. There will be flexibility in scheduling, and parents will be given the option for these times to remain the same over the course of the 12 weeks or to change as schedules require.

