## Discussion

With the results from this study, we will determine whether or not a home-based wellness coaching program is feasible for use with female children. A secondary outcome will be to evaluate the possibility of change in health-related psychosocial, behavioral, and biomedical outcomes through each intervention condition. Since this is a feasibility trial, we want to assess outcomes for both of the treatment arms of the intervention. The intervention conditions will be evaluated for future potential, so that they may be integrated most effectively into a future fully powered randomized controlled trial. For this type of intervention, we will recruit participants through the parents, who are concerned, at least to some extent, with the health of their children. As such, it may not be an ethical or viable option to offer no type of intervention. Because of this, our active comparison group represents general health behavior mentoring but does not focus specifically on physical activity and nutrition. This condition of health behavior mentoring used in our active comparison group, while not precisely current practice, represents more of a “standard” than the hands-on approach used in the HEPA intervention arm. Since this is a new combination of a one-on-one wellness coaching intervention delivered within the home setting to girls, there is no current literature available regarding effect sizes needed for future power calculations. As such, we will assess the preliminary impact on health-related outcomes to more appropriately inform a future fully powered trial. Using a 6-month follow-up assessment will allow us to evaluate the feasibility of having participants return to the laboratory following a no-contact period, as well as the potential for lasting impacts resulting from the study.

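### Adverse effects are a primary outcome, but the coach is the only named source, none is named after week 12, and satisfaction is measured once with no stated handling of families who stop early

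*Protocol article*

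**What the plan says.** The primary objective, at the end of the Background, lists seven feasibility outcomes. Two matter here: adverse effects associated with the intervention, and the satisfaction of participants and parents.

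Under Intervention delivery feasibility and acceptance, the article says how each is obtained. For harms: "Any adverse effects related to intervention delivery will be collected via coach report". For acceptance: "parent and participant satisfaction questionnaires, which will be completed during a post-intervention interview". No other source is named for either. The same section takes session completion "of each participant via coach self-report, following each session".

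On timing, the abstract states: "Trained female wellness coaches will conduct weekly hour-long home visits for 12 consecutive weeks". Study design places the last assessment 6 months after baseline, and the Discussion says that this visit will "evaluate the feasibility of having participants return to the laboratory following a no-contact period". Laboratory assessment procedure itemises nine visit components. None is an adverse-event question or a satisfaction measure.

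Two further statements bear on the point. The Background notes that "overweight and obese adolescent girls are more likely than healthy weight girls to use dysfunctional methods to try to control their weight". Wellness coaching interventions says that "at least one parent is always present in the home during the session".

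**The concern.** Three features of the harms measure point the same way.

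- **Source.** The only named reporter is the person whose sessions are being evaluated. She visits for about an hour a week. An event between visits reaches the record only if she notices it or is told of it.
- **Scope.** The outcome list covers effects associated with the intervention. The measurement sentence covers effects related to its delivery. An injury during a session fits both. Restrictive eating or distress that appears on other days may fit only the first. The Background itself names dysfunctional weight control as a problem in overweight and obese adolescent girls.
- **Time.** The named source ends with coaching, while the girls are followed for about as long again.

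Satisfaction has a related weakness. It is measured once, after the intervention, and families who stop early are the ones most likely to be absent.

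The article makes a fully powered trial conditional on feasibility. A report of no adverse effects and a well-received programme would weigh in that decision, for children aged 8 to 13. Both statements would depend partly on who was asked and when.

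**Working it through.** The article gives no harm rate, dropout rate, satisfaction threshold or sample-size calculation for these outcomes, so there is no figure of its own to reproduce. The check is one of coverage, followed by two illustrations on assumed values.

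**1. Coverage of follow-up by the named harms source**

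Inputs: 12 weeks of coaching (abstract); 6 months of follow-up, about 26 weeks (Study design).

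- Covered: 12/26 = 46%.
- No named source: (26 − 12)/26 = 14/26 = 54%.

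This is calendar time, not exposure time. The 14 weeks contain no intervention contact, so the risk of a related event is probably lower in them.

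**2. What partial coverage could do to the count**

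Inputs: 40 girls (Study population). Assumed: a 6-month risk p of 2%, 5% or 10% per girl; half of it in the coached period; every event in that period recorded.

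Formulas: with full coverage, P(at least one event recorded) = 1 − (1 − p)^40. With the coached period only, it is 1 − (1 − p/2)^40.

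| Assumed p | Full coverage | Coached period only |
|---|---|---|
| 2% | 1 − 0.98^40 = 55% | 1 − 0.99^40 = 33% |
| 5% | 1 − 0.95^40 = 87% | 1 − 0.975^40 = 64% |
| 10% | 1 − 0.90^40 = 99% | 1 − 0.95^40 = 87% |

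The even split drives the size of the loss. If all the risk fell in the coached period, timing would cost nothing and the two columns would be equal. Working the other way, the table assumes that the coach records every event in her period; events that she does not learn of would lower the right-hand column.

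**3. Satisfaction with non-response**

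Inputs: 40 randomized. Assumed: 10%, 20% or 30% drop out and do not answer; about 90% of the m who answer are satisfied, giving s families.

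Formulas: observed = s/m; worst case = s/40 (no non-responder satisfied); best case = (s + 40 − m)/40 (all of them satisfied).

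| Dropout | m | s | Observed | Worst case | Best case |
|---|---|---|---|---|---|
| 10% | 36 | 32 | 89% | 32/40 = 80% | 36/40 = 90% |
| 20% | 32 | 29 | 91% | 29/40 = 72.5% | 37/40 = 92.5% |
| 30% | 28 | 25 | 89% | 25/40 = 62.5% | 37/40 = 92.5% |

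The observed figure hardly moves across the three rows, while the range compatible with it widens from 10 to 30 percentage points. The observed percentage alone does not show this.

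**The case against.** The strongest reply is that this is a condensed article. It does not say that coach report is the only route for harms, and adverse-event procedures or contact with early leavers may be set out in the full protocol. That has force against any claim that harms are ignored. It has less force against what is printed: the article does not merely omit the source of a primary outcome but states one, and it itemises the visit content without a harms question. The difference in scope between the two wordings does not depend on silence at all.

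Second, months 3 to 6 are free of intervention, so exposure is concentrated in the covered weeks. This stands, and the 54% should not be read as lost exposure. Late or delayed effects remain possible.

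Third, the girls' wellbeing is not unobserved. Child and parent-proxy quality of life, BMI and body composition are measured at both later visits, and coaches discuss emotions and everyday difficulties during sessions. This also stands. A reader might infer that families are never asked about the girls' health; the article does not support that. But none of these measures is listed as a harms measure, and a quality-of-life score does not record an event.

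Fourth, disengagement is already visible, because sessions delivered and assessments completed are themselves primary outcomes. Retention would therefore be reported beside satisfaction. What would be missing is the view of those who left.

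**Conclusion.** The point holds in a limited form. Following the article as written could under-count harms: the deliverer is the sole named source, none is named for about 14 of 26 weeks, no harms question is listed at the later visits, and the measured item is narrower than the listed outcome. The size cannot be derived from the document. With an assumed 5% risk split evenly over time, the chance of recording any event in 40 girls falls from 87% to 64%; if all the risk lay in the coached weeks, timing would cost nothing.

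For satisfaction the point is a risk, not a stated defect. Its size depends on dropout. At an assumed 20%, the range over all 40 girls is 72.5% to 92.5%.

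Three stronger readings are tempting and are not supported:

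- That fidelity is coach-reported only. The coach self-report phrase is attached to session completion; the fidelity sentence names no source.
- That the coach decides which events are related. The text assigns that judgement to nobody.
- That families who stop early are excluded from the interview. The text neither excludes nor includes them.

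**What to change.** **Harms**

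- At the existing 3- and 6-month visits, ask parent and girl one standard open adverse-event question and record every event regardless of attribution.
- Report events per randomized girl by arm, beside the coach reports, with the source shown.
- Reconcile the outcome list in the Background with the measurement sentence, so that the outcome and what is collected have the same scope.

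**Satisfaction**

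- Send the same questionnaire to families who stop early.
- Report the number responding out of all randomized, with best- and worst-case bounds for non-response as in the working.

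**Cost.** A few minutes per visit and a mailed or emailed form. Blinding needs care: answers may reveal the arm, and the article has the same research assistant take the anthropometric measurements at every assessment, so a disclosure at 3 months would carry over to 6 months. A sealed written form, or a question put by someone who does not assess outcomes, would avoid this. Reported harms will probably rise somewhat and reported satisfaction fall; both should be expected when the results are read.

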#### Health-related outcome assessment feasibility

The feasibility for assessing health outcomes will be determined by calculating the number and percentage of participants who complete the post-intervention and follow-up health assessments. These metrics will allow us to understand whether laboratory assessments can be completed during the scheduled timeframe and whether it is feasible for this sample to return to the laboratory following a no-intervention follow-up period.

### Secondary outcome evaluation

The health-related psychosocial outcomes include changes in child quality of life (measured through the PedsQL instrument), as well as self-efficacy and enjoyment of physical activity and fruits and vegetables. Health-related behavioral outcomes for this study are the change in daily physical activity and sedentary time (minutes per day, as measured by accelerometer), steps per day, and fruit and vegetable intake. Health-related biomedical outcomes include change in BMI *Z*-score from baseline, as well as changes in body fat percentage, waist circumference, blood pressure, pulmonary function, and systemic inflammation.

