## Background

Approximately one out of every three children in the USA is overweight or obese [1]. Obese children are more likely than healthy weight children to have detrimental health outcomes, including high blood pressure, dyslipidemia, type 2 diabetes, and psychosocial problems [2–4]. Additionally, overweight and obese children are at a significantly greater risk of adult obesity, compared to children at a healthy weight [5]. This tracking of obesity into adulthood may lead to the development of more severe health outcomes [6]. In addition to health problems related to obesity, there is considerable financial burden associated with childhood obesity; medical costs from youth into adulthood are estimated at approximately $19,000 more per obese child, in comparison with healthy weight children [7]. As such, early interventions that target obesity treatment and prevention are warranted.

Successful childhood obesity interventions aim to regulate body fat and weight, while allowing for further growth [8] in ways that promote the persistence of healthful behaviors throughout the developmental years [9]. The goal is typically not weight loss but rather to achieve increases in height while slowing weight gain. Secondary prevention measures may focus on reducing the impact of childhood obesity by slowing or reversing the weight gain through the building of healthful behaviors. Secondary prevention techniques may include self-efficacy and skill-building for behaviors related to nutrition and physical activity [10]. Given that obesity may result from prolonged positive energy imbalance, interventions typically promote increased energy expenditure or appropriately balanced caloric intake, which can each be considered independent avenues to improve obesity outcomes. It is critical that childhood obesity interventions are handled with “kid gloves,” in that great care is taken to not stigmatize the individuals, and to ensure that quality of life is considered alongside weight status and healthful behaviors.

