### Study population

Participants for this study are 40 females aged 8 to 13 years. All girls will have a body mass index (BMI) at or above the 85th percentile (overweight or obese) of gender-specific, age-adjusted growth charts and must reside within 20 miles of Manhattan, KS (Kansas State University). Exclusion criteria require that the girls do not have developmental delays, psychiatric problems, or any illness, injury, or condition that prevents them from participating in moderate-to-vigorous physical activity. Finally, the participants cannot be taking weight-altering medication or be participating in any other weight control program. There will be no inclusion/exclusion criteria related to socioeconomic status or ethnicity. Parental consent and child assent will be obtained from all participants prior to their participation in the study. Kansas State University Institutional Board of Human Ethics approval has been obtained, and all study methods will comply with the Declaration of Helsinki.

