### Randomization

Rolling recruitment will be implemented, and participants meeting the inclusion criteria will be block-randomized using an online randomization program into one of two wellness coaching conditions, in blocks of four, with a 1:1 allocation ratio. The principal investigator will oversee the randomization process and will keep allocation concealed until baseline assessments have been completed. Research assistants collecting assessment data will be blinded to group randomization over the course of the study. Blinding of the study participants to their group assignment will not be possible due to the nature of the intervention itself, but participants will not know their assigned condition until after baseline assessments.

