### Statistical analyses

Feasibility outcomes (retention, participation, compliance, etc.) will be assessed through descriptive statistics. Data will be analyzed using SPSS statistical software (version 22.0). Despite a lack of power to detect differences between the two intervention arms, we will perform a preliminary assessment of change in psychosocial, behavioral, and biomedical outcomes. There will be an emphasis on presenting the descriptive statistics for health-related outcomes, with summary statistics and confidence intervals reported. An alpha of 0.05 will be used for all analyses, and effect sizes for future sample size calculations will be calculated on potential primary outcome measures by subtracting baseline means from post-intervention and follow-up means, divided by the appropriate pooled standard deviation. Where appropriate, results will be presented as point estimates, supported by 95 % confidence intervals.

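### The stated effect size is a pre-post change with no comparison-arm term, so for waist circumference and blood pressure it counts normal growth as change

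*Protocol article*

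**What the plan says.** - **Outcomes and scales.** Secondary outcome evaluation lists "change in BMI *Z*-score from baseline", "as well as changes in body fat percentage, waist circumference, blood pressure, pulmonary function, and systemic inflammation". The anthropometrics section converts BMI to CDC age-sex percentiles. The same section describes waist as a tape measurement, and the blood pressure section describes plain systolic and diastolic readings. Neither names an age, sex or height reference. The pulmonary function section does plan a comparison of spirometry values with norms for age, height, ethnicity and sex.
- **Effect size.** Statistical analyses says effect sizes for future sample size calculations will be obtained "by subtracting baseline means from post-intervention and follow-up means, divided by the appropriate pooled standard deviation". They are for potential primary outcome measures, which are not named. The section concedes a lack of power between arms and puts the emphasis on descriptive statistics and confidence intervals.
- **Focus on each arm.** The Discussion says "we want to assess outcomes for both of the treatment arms of the intervention" and describes the secondary aim as evaluating possible change under each condition.
- **Population and timing.** "Participants for this study are 40 females aged 8 to 13 years", randomized "in blocks of four, with a 1:1 allocation ratio", with assessments at baseline and at 3 and 6 months.
- **Growth is expected.** The Background says successful interventions "aim to regulate body fat and weight, while allowing for further growth".

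**The concern.** The effect-size formula subtracts a baseline mean from a later mean. In growing children this difference contains two parts, the effect of the intervention and the growth that would have happened anyway. The article deals with growth for BMI by using a Z-score, but names nothing comparable for waist circumference or blood pressure. Both arms are active, so neither shows growth alone, and a figure computed arm by arm cannot separate the two parts.

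For waist and blood pressure a lower value is better. Growth that raises them therefore works against a real benefit and may hide it. This affects the descriptive change reported for each condition. It also affects any effect size for these outcomes that is carried into the sample size of the next trial. The Discussion says that no published effect sizes exist for this model, so the trial's own figures are the intended planning input.

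**Working it through.** The article states no effect size, SD or growth rate, so there is no figure to reproduce. The check takes the stated formula and asks what it returns when the intervention does nothing.

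**1. The formula under zero intervention effect.** Let *g* be the growth drift between two visits, in cross-sectional SD units (taking the pooled SD as cross-sectional).

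- Stated formula: d = (later mean − baseline mean) / SD = g + 0 = g.
- Between-arm difference in change: (g + 0) − (g + 0) = 0 in expectation, because randomization gives both arms the same expected growth.

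**2. Size of the drift.** Growth rates and SDs are assumptions. Drift = growth / SD.

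| Outcome | Assumed six-month growth | Assumed SD | Smallest | Largest | Half, at 3 months if linear |
|---|---|---|---|---|---|
| Waist | 1 to 2 cm | 8 to 12 cm | 1/12 = 0.08 | 2/8 = 0.25 | 0.04 to 0.13 |
| Systolic pressure | 0.5 to 1.0 mmHg | 9 to 11 mmHg | 0.5/11 = 0.05 | 1.0/9 = 0.11 | 0.02 to 0.06 |

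**3. Masking, illustrated for waist.** Suppose a true benefit of −1.5 cm and an SD of 10 cm, both assumed. The true effect is −1.5/10 = −0.15 SD. With growth of 1 to 2 cm, the formula gives (−1.5 + 1)/10 = −0.05 to (−1.5 + 2)/10 = +0.05. The benefit would look like no change.

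**4. Confidence intervals for change within one arm.** With 40 girls allocated 1:1, n = 20 per arm. Assume a baseline-to-follow-up correlation r of 0.8 to 0.95. The SD of change is √(2(1 − r)) in cross-sectional SD units. The noncentrality of the paired t statistic is g√20 / √(2(1 − r)); for example, g = 0.20 and r = 0.9 give 0.20 × 4.47 / 0.447 = 2.0. The table gives the chance that a 95% interval excludes zero when the intervention does nothing (nominal 5%).

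| Drift g | r = 0.8 | r = 0.9 | r = 0.95 |
|---|---|---|---|
| 0.05 | 6% | 8% | 10% |
| 0.10 | 10% | 16% | 27% |
| 0.20 | 27% | 48% | 77% |
| 0.30 | 52% | 81% | 98% |

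The last row lies above the range in step 2. Correlations below 0.8 would give smaller percentages.

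**5. Precision of the alternative.** In cross-sectional SD units, the standard error of one arm's mean change is √(2(1 − r)/20), that is 0.14 at r = 0.8 and 0.07 at r = 0.95. For the between-arm difference in change it is √2 times larger, 0.20 and 0.10. The growth term is removed at the price of an interval about 1.4 times as wide.

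**The case against.** Several objections have force.

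- **Lung function.** A reader might infer that FVC and FEV1 are also to be analysed as raw volumes, so that growth would create a false benefit. The article does not support that, because it plans comparison with norms for age, height, ethnicity and sex. What remains is narrower: neither the outcome list nor the effect-size sentence says whether change is taken in litres or on the norm-referenced scale.
- **Within-arm analysis.** A reader might also infer that only within-arm change will be analysed. The article never says so. The trial is randomized to compare two arms, and a between-arm contrast of change is not excluded. The arm-by-arm reading is a fair inference from a formula without a comparison-arm term and from the Discussion's focus on each condition, but it is an inference.
- **Use in the next trial.** The outcomes that will receive effect sizes are not named. Nothing shows that waist or blood pressure is among them, and BMI is already a Z-score.
- **An article condenses.** Analysis scales are commonly left to a fuller document, so silence on the scale for waist and blood pressure would not be a fault by itself. The effect-size formula is different: it is written out, and the point rests on what it says.
- **Size and consequence.** All magnitudes rest on assumed growth and SDs. The blood pressure drift is small even at six months, and is small beside the standard errors in step 5. The primary outcomes are feasibility metrics, and no efficacy conclusion is planned.

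These objections narrow the point and lower its weight. They do not remove it, because the stated formula cannot distinguish growth from intervention effect.

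**Conclusion.** The point holds for waist circumference and blood pressure. As written, the effect size counts growth in girls aged 8 to 13 as change, one for one, while BMI alone among the body-size measures is given a growth-referenced scale. The mechanism follows from the formula and needs no outside figure. The direction, masking of benefit, holds wherever growth raises the measure.

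The size is uncertain. Under the assumed values it is roughly 0.08 to 0.25 SD for waist and 0.05 to 0.11 SD for systolic pressure at six months, and about half that at three months if growth is linear. The harm is confined to the descriptive change in each arm and to any planning effect size taken from these outcomes. The feasibility aims are untouched. It is worth changing because it is cheap, not because it endangers the trial.

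**What to change.** 1. In Statistical analyses, define the planning effect size as the between-arm difference in change from baseline, over a named SD, with its 95% confidence interval. Common growth then cancels in expectation without any reference data.
2. In Secondary outcome evaluation and Statistical analyses, define change in waist as change in waist-to-height ratio or in an age-sex Z-score, and change in blood pressure as change in an age-sex-height Z-score. Keep the raw values as description.
3. State that change in FVC and FEV1 is computed on the norm-referenced scale already planned in the pulmonary function section.
4. Where change is still shown for each arm, say that it includes growth unless the scale is growth-referenced.

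The cost is a few sentences and a little programming. Sex is fixed by eligibility, height is measured at each assessment, and age is already needed for the BMI Z-score, so no new data are required. The between-arm estimate will have a wider interval, by a factor of about 1.4 with equal arms. Growth-referenced scales remove only the growth expected in the reference population, so step 1 is the main correction and steps 2 and 3 support it.
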